# Methodology and recruitment for a randomised controlled trial to evaluate the safety of *wahakura* for infant bedsharing

**DOI:** 10.1186/1471-2431-14-240

**Published:** 2014-09-28

**Keywords:** Sudden Unexpected Death in Infancy, Sudden Infant Death Syndrome, Infant, Sleep, Prevention, Culture, Protocol, Indigenous, Bedsharing, Co-sleeping

## Abstract

**Background:**

Sudden Unexpected Death in Infancy (SUDI) has persistent high rates in deprived indigenous communities and much of this mortality is attributable to unsafe sleep environments. Whilst health promotion worldwide has concentrated on avoidance of bedsharing, the indigenous Māori community in New Zealand has reproduced a traditional flax bassinet (*wahakura*) designed to be used in ways that include bedsharing. To date there has been no assessment of the safety of this traditional sleeping device.

**Methods/Design:**

This two arm randomised controlled trial is being conducted with 200 mother-baby dyads recruited from Māori communities in areas of high deprivation in the Hawkes Bay, New Zealand. They are randomised to *wahakura* or bassinet use and investigation includes questionnaires at baseline (pregnancy), when baby is 1, 3, and 6 months, and an overnight video sleep study at 1 month with monitoring of baby temperature and oxygen saturation, and measurement of baby urinary cotinine and maternal salivary oxytocin. Outcome measures are amount of time head covered, amount of time in thermal comfort zone, number of hypoxic events, amount of time in the assigned sleep device, amount of time breastfeeding, number of parental (non-feed related) touching infant events, amount of time in the prone sleep position, the number of behavioural arousals and the amount of time infant is awake overnight. Survey data will compare breastfeeding patterns at 1, 3, and 6 months as well as data on maternal mind-mindedness, maternal wellbeing, attachment to baby, and maternal sleep patterns.

**Discussion:**

Indigenous communities require creative SUDI interventions that fit within their prevailing world view. This trial, and its assessment of the safety of a *wahakura* relative to a standard bassinet, is an important contribution to the range of SUDI prevention research being undertaken worldwide.

**Trials registration:**

Australian New Zealand Clinical Trials Registry: ACTRN12610000993099 Registered 16^th^ November 2010

## Background

Sudden Unexpected Death in Infancy (SUDI) is the biggest single component of post neonatal death in the developed world. The unexplained portion of these deaths, typically called Sudden Infant Death Syndrome (SIDS), has been defined by the sudden death of an infant in sleep, which is unexplained after the review of the clinical history, post-mortem findings, and examination of the circumstances of death
[1]. The term SUDI was developed to include causes of death such as “positional asphyxia” and “undetermined”, which are often used when known risk factors are present even though the contribution of the risk factors to death is unclear. The term SUDI encompasses SIDS and these more uncertain scenarios
[2] and reflects the increasing focus on identifying and reducing unsafe sleep environments as a strategy to reduce post-neonatal mortality
[3].

### SUDI

In New Zealand, the SUDI mortality rate over the 2003–2007 period was 1.1 per 1000 live births, with between 50–85 babies dying annually
[3]. Sixty two percent of these deaths occurred in the indigenous Māori community, who comprised only 15% of the population. The SUDI rate for Māori during this time was 2.34 deaths per 1000 live births; that is, five times the rate of European New Zealanders (non-Māori, non-Pacific, non-Asian) at 0.52 deaths per 1000 births
[3]. Indigenous peoples in other countries have similar disparities, for instance, Native American and Alaskan populations in the United States
[4], Inuits in Nunavut, Canada
[5], and Western Australian Aboriginals
[6] have SUDI rates between 3–8 times the rates of their non-indigenous counterparts.

SIDS rates decreased markedly around the world with the introduction of the back sleeping position; in New Zealand, SIDS rates fell from 4.4 per 1000 live births in 1988
[7] to 1.6 per 1000 live births in 2002
[3]. The peak age for SUDI in New Zealand moved from three months of age in the 1990s to one to two months of age in the period, 2003–2007. Similar trends were identified elsewhere
[8]. Over this time there was also a marked widening of disparities between social groups and SUDI became increasingly associated with poverty, poor education and maternal smoking
[8–10].

### Bedsharing

Many case control studies have identified conditions in which bedsharing is associated with increased risk of sudden infant death. The most consistent finding is that exposure to cigarette smoke in utero greatly increases the risk of SIDS when bedsharing
[11, 12]. Other contributing factors include excessive maternal tiredness, infant overheating and household overcrowding
[12], the use of sedative drugs
[13], or alcohol
[14, 15] and maternal obesity
[16]. In the absence of any of these other factors, there is a suggestion that although bedsharing per se has some risk for babies under the age of 14 weeks
[15], the risk is significantly smaller than where there is smoking during pregnancy.

### Smoking

Maternal smoking in pregnancy is recognised as the primary cause of increased vulnerability when bedsharing. A decreased arousability to hypoxia from fetal exposure to passive smoking may well be the mechanism that leads to this increased risk
[17–19]. To add to the complexity, bedsharing is also a common and valued childcare practice in many cultures, including Māori and Pacific families in New Zealand
[20] and is seen in many cultures as developing and maintaining a sense of ongoing connection to the infant
[21, 22] as well as facilitating breast feeding
[23–25]. Māori women however, have high rates of smoking and Māori women from communities of high deprivation in Auckland, New Zealand’s biggest city, have a prevalence of cigarette smoking in pregnancy of 53%
[26]. Despite vigorous efforts to decrease smoking in pregnancy
[27] there has been limited success
[28]. Likewise, efforts by health professionals, the Ministry of Health and coroners to discourage bedsharing do not appear to have had any impact as 65% of Māori mothers in Auckland bedshare with their infants for some part of the night
[26]. In addition, a mortality review of the years 2000 to 2009 in the same city showed that 64% of all SUDI cases were found dead in a shared bed
[29]. Nationally, 43% of SUDI deaths occurred when bedsharing
[3], and an increasing proportion of these deaths are now labelled accidental suffocation
[30]. Unfortunately, mortality review data collection around risk factors associated with these deaths is incomplete in New Zealand and it was not possible to identify the contribution of factors such as smoking in pregnancy or alcohol consumption on the night of death.

### A culturally derived intervention

In response to this combination of high risk behaviours and the cultural value of bedsharing as an important component of infant care practices
[31–33], the Māori community has developed the *wahakura*. The *wahakura* is a woven flax bassinet with a thin, firm mattress designed specifically to create a separate sleeping surface in the shared sleeping space. It is distributed with a set of ‘safe sleeping rules’
[34] derived from the recommendations of the New Zealand Ministry of Health. Its acceptability to Māori comes from its community origin and its Māori nature and appearance
[35].

*Wahakura* are increasingly being used by families across the country and in some places are distributed by District Health Boards
[36], and thus there is an imperative to establish their safety profile. To date, there are no studies of the effect of the use of the *wahakura* in the context of bedsharing on infant or adult sleeping behaviour; nor of what effect the professional interactions associated with the handover of *wahakura* might have on wider parental behaviour like the recall of safe sleeping advice, parental response to infant needs, changes in smoking behaviour or attachment behaviours; or of the *wahakura* on infant behaviour (e.g. breastfeeding, sleeping pattern).

Furthermore, as we learn more about the complex interaction between biology, environment and culture, and how mothering is often at the intersection of these concepts, a fuller understanding of the effects of such interventions would usefully measure some of these variables including salivary oxytocin levels
[37, 38], ‘mind-mindedness’ (the mother’s ability to think about her infant’s emotions, thoughts and needs) and post-natal mood, all of which have important effects on parenting behaviour
[38–40].

### Aim of the study

To determine the safety and other benefits, or harm, from providing either a *wahakura* or bassinet to families attending a mainly Māori midwifery service from geographical areas of high deprivation in an urban setting in New Zealand. We intend to compare physiological and behavioural measures of infants in the two sleep environments, such as temperature and desaturation events, differences in infant head covering events and breastfeeding time and whether allocation of sleep device impacts on time spent bedsharing.

In addition, we will look at how the use of a *wahakura* relates to other issues of safety in the infant period, to ‘mothering’, mind-mindedness, a sense of family, maternal post-partum depression and to cultural identity.

## Methods/Design

### Overall study design

Ethical approval to conduct this study has been granted by the New Zealand Central Region Ethics Committee (CEN/10/12/054).

This is a randomised controlled trial of *wahakura* versus bassinet to test the following hypotheses:That the use of a *wahakura* is not significantly different in terms of thermal environment, head covered duration, episodes of oxygen desaturation, or total sleep duration, than infants sleeping in a separate bassinet in the same room.That the ‘*wahakura* group’ spends less time per night bedsharing on the same bed surface than the ‘bassinet group’.That the use of a *wahakura* is associated with significantly increased breastfeeding episodes, breastfeeding duration, and more parental “looking and touching” episodes.That use of a *wahakura* is associated with greater involvement of the extended family, more attention to other issues of safety, and a greater sense of connection to familyThat the use of the *wahakura* promotes maternal and extended family mind-mindedness and development of individual, family, and cultural identity.

Participants will be randomized to receive a *wahakura* or bassinet and the above aspects will be studied using a combination of questionnaires and an overnight sleep study with video, temperature and oxygen saturation measurement. Baby urine (for cotinine) and maternal saliva (for oxytocin) will be collected, and a recording will be made of mothers talking about their feelings about their baby.

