### Head covering

The proportion of babies having an overnight sleep with a head covering episode by blankets was 1/37 and so, in order to detect a difference of 15% between babies sleeping in wahakura and cots with 80% power using the 5% level of significance, two groups of 88 babies would be needed.

Assuming the proportion of babies having an overnight sleep with a head-covering episode by blankets will be 3% when sleeping in a bassinette, 88 babies per group are required to detect a difference of 15% between babies sleeping in wahakura and cots with 80% power using the 5% level of significance.

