#### Data analysis

The data will be analysed using modified intention to treat, including only those who completed at least one of the 1, 3 or 6 month visits. Chi-squared tests or Student t-tests will be used to compare the outcomes in the two groups. A per protocol analysis will also be carried out to estimate differences in the outcome variables in those who were compliant with the sleeping arrangement to which they were assigned.

This study will also provide an opportunity to examine factors associated with breastfeeding and sleep practices in a disadvantaged group. The breastfeeding data will be analysed using a discrete time model.

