## Discussion

As far as we are aware, there are no other studies of this nature being performed anywhere in the world. SUDI prevention is an important area of research in the Western world, and the advent of ongoing, extremely high rates of SUDI in communities of deprivation, including indigenous communities, has not been effectively addressed to date. In addition, the *wahakura* has not been developed by the scientific community, nor has it arisen from the wider health sector. It is a cultural reclamation of an item used traditionally in Māori society in the effort to continue the valued practice of bedsharing, while maintaining the safety of the infant. We will assess the risks and benefits around the *wahakura*, to establish whether it might be able to be recommended as a safe sleeping device for prevention of SUDI. Whilst it has been suggested there is some ‘face validity’
[61] and there is support in the high risk community for this device, there is no empirical evidence as yet assessing its safety. This study seeks to provide exactly that.

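### The safety hypothesis is a claim of no difference, judged by tests of difference with no margin, so a non-significant result counts in its favour

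*Protocol article*

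**What the plan says.** Under Overall study design, hypothesis 1 is that wahakura use "is not significantly different in terms of thermal environment, head covered duration, episodes of oxygen desaturation, or total sleep duration" from sleep in a separate bassinet in the same room. The other four hypotheses are directional; only this one predicts no difference.

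Under Data analysis, the stated method is that "Chi-squared tests or Student t-tests will be used to compare the outcomes in the two groups", in a modified intention-to-treat set, with a further per-protocol analysis. Under Contamination, the safety outcomes (head covering, peripheral temperature, oxygen saturation) are to be analysed by the device actually used.

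The sample size is also built on detecting a difference. For head covering the article plans "to detect a difference of 15% between babies sleeping in wahakura and cots with 80% power", starting from 3% in bassinets. It aims for complete 1-month data on 100 babies per group.

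The Discussion gives the use of the result: "to establish whether it might be able to be recommended as a safe sleeping device for prevention of SUDI". No equivalence or non-inferiority margin appears anywhere, and no rule based on a confidence limit.

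**The concern.** A test of difference puts the burden of proof on showing harm. When the hypothesis itself is that there is no significant difference, failing to show harm becomes the confirming result. Anything that reduces precision then favours the hypothesis: few events, lost video or oximetry, noisy coding. A trial that learned little would look the same as one that showed the devices to be alike.

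This matters because the question is infant safety and the device is already being distributed. The error falls on the infants' side. It is also fixed in the printed hypothesis and the named tests, so it is not a detail that a separate analysis plan would simply fill in.

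**Working it through.** **Inputs.** Control proportion 3% (Head covering section: "Assuming the proportion of babies having an overnight sleep with a head-covering episode by blankets will be 3% when sleeping in a bassinette", from an earlier study in which the proportion with a "head covering episode by blankets was 1/37"). Planning difference 15 points. Power and level: "with 80% power using the 5% level of significance"; sidedness is not stated, so two-sided is assumed. Group size 100 with 1-month data (Total numbers required).

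**Scale.** These figures concern the proportion of babies with at least one head-covering episode, the only head-covering scale with planning figures. Hypothesis 1 and the primary outcome concern duration, for which no mean or SD is given.

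**1. The plan's own figure.** The article says "88 babies per group are required to detect a difference of 15% between babies sleeping in wahakura and cots". With n = [1.96·√(2·p̄·q̄) + 0.8416·√(p₁q₁ + p₂q₂)]² / d², p₁ = 0.03, p₂ = 0.18, p̄ = 0.105:
- n = (1.96 × 0.4335 + 0.8416 × 0.4204)² / 0.15² = 1.448 / 0.0225 = 64.4, so 65 per group; 78 with continuity correction.

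The stated 88 does not follow from its inputs. It errs on the large side (88 per group gives about 91% power for 3% v 18%). This is a separate matter, and nothing below depends on it.

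**2. Chance of a non-significant result, 100 per group, 3% in bassinets.** Normal approximation for a true 9%: z = (0.06 × √100 − 1.96 × √0.1128) / √0.111 = (0.600 − 0.658) / 0.333 = −0.175, so power is 43% and the chance of non-significance 57%. Exact binomial enumeration of the chi-squared test gives:

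| True wahakura rate | Uncorrected | Continuity-corrected |
|---|---|---|
| 6% | 85% | 91% |
| 9% | 57% | 70% |
| 18% (planning value) | 4% | 7% |

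**3. What such a result looks like.** For 9/100 v 3/100, χ² = 200 × (3×91 − 9×97)² / (12 × 188 × 100 × 100) = 3.19, p = 0.074. Wilson limits are 4.8% to 16.2% and 1.0% to 8.5%. The Newcombe interval for the difference is:
- lower: 6.0 − √(4.2² + 5.5²) = −0.9 points (from unrounded limits)
- upper: 6.0 + √(7.2² + 2.0²) = +13.5 points

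This is not significantly different, yet compatible with a rise of 13 points on a base of 3%.

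**4. What a margin rule would do instead.** The rule declares non-inferiority if the upper Newcombe 95% limit lies below the margin. Exact enumeration, 100 per group, 3% in bassinets:

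| True wahakura rate | Passes at 10 points | Passes at 15 points |
|---|---|---|
| 3% (equal) | 93% | over 99% |
| 6% (doubling) | 54% | 94% |
| 9% (tripling) | 18% | 66% |

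The 15-point rule passes a tripling more often (66%) than the uncorrected significance test misses it (57%). Only a tighter margin improves protection.

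**5. Joint success.** For thermal comfort at 75% in both arms, power to exclude a 20-point loss is 91%. If the two outcomes were independent, joint power with the 10-point head-covering margin would be 0.933 × 0.913 = 85%. The article gives no planning figures for desaturation or head-covered duration, so power across all safety outcomes is unknown.

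**The case against.** **No decision rule is written.** A reader might infer that a tripling of head covering would be passed as safe more often than not. The document does not support that as a statement of fact. Nowhere does it say that p above 0.05 leads to a declaration of safety. The aim covers harm as well as benefit, the Discussion speaks of weighing risks and benefits, and a condensed article may leave interval reporting to the full plan. What stands is narrower: the hypothesis as worded is confirmed by non-significance, and no other criterion is offered.

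**The figures are on a different scale from the hypothesis.** This is correct. The 57% applies to the planning proportion and cannot be carried over to duration.

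**Cross-over.** A reader might infer that device cross-over also biases towards a finding of safety. The Contamination section partly answers this by analysing the safety outcomes by device used. That limits dilution, but it gives up the randomised comparison and does not move the burden of proof.

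**The effect size is chosen.** The tripling is illustrative; at the article's own 15-point difference only about 4% of results would be non-significant. That is true, but 3% v 18% is a six-fold rise, and nothing in the document says that smaller rises are acceptable.

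**Conclusion.** The concern holds for the form of the hypothesis and the missing criterion. A safety claim is framed as absence of significance, tested only with tests of difference, and intended to inform a recommendation. Confidence in that is high, since it rests on the printed text.

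Its size can be shown only for the proportion with a head-covering episode: with 3% in bassinets and 100 per group, a true 9% goes undetected 57% of the time (70% corrected) and a true 6% goes undetected 85% (91% corrected). These figures assume equal groups and two-sided testing at 5%. Grouping by device used could make the groups unequal, which would usually lower power further. For duration and desaturation the same logic applies, but no rate can be given.

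**What to change.** - Restate hypothesis 1 as non-inferiority for the safety outcomes: head covering, thermal environment and desaturation.
- Conclude that the wahakura is no worse than a bassinet on an outcome only if the harm-side 95% confidence limit excludes a margin fixed and justified by the clinical team before the data are analysed. For proportions, a Newcombe or Miettinen-Nurminen interval is suitable. Otherwise report the interval and state that safety is not established.
- Do not use the 15-point planning difference as the head-covering margin. A detectable difference is not an acceptable harm. A margin of about 10 points illustrates what 100 per group can support (93% power if rates are equal), though it would still pass a doubling 54% of the time. The choice remains a clinical judgement.
- Give a margin for duration on its own scale, since that is the primary outcome.
- Report the as-randomised analysis beside the planned as-used analysis, and require the two to agree before a non-inferiority conclusion is drawn.

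**Cost.** Rewording the hypothesis and analysis text, and clinical work on the margins. No increase in enrolment is asked for, but adequate power to succeed on every safety outcome cannot be promised. The trial may end inconclusive where it would otherwise have reported no difference.

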### Participants and recruitment

Recruitment and data collection will be done in Hawke’s Bay, a region in the North Island of New Zealand with two urban areas, Hastings and Napier. Mothers booking into two mainly Māori midwifery services will be informed of the study by their midwife, and asked if they wish to participate.

Should the mother express interest, then the study researcher will either meet her at the clinic venue or visit her at home to explain the study in more depth, offering further time to discuss the study with the extended family. An information sheet directly aimed at the extended family, written in an appropriate English and Māori format will describe the study. Should the mother agree to be involved, written informed consent will be obtained and baseline questionnaires completed. Participants will be randomised to a sleeping device (randomisation in blocks by parity and deprivation quintile), with either a *wahakura* or a bassinet given to the family. Anonymous demographic information (age, ethnicity, parity and deprivation score)
[41] will be collected for those who decline to participate in the study.

A birth congratulations card will be sent to the family shortly after the birth of the baby as a reminder to use the appropriate sleep device, and telling them that they will be contacted to organise a home sleep study when the baby is 1 month old. Participants will be given a $50 grocery voucher gift after the 1 month sleep study, and a $25 voucher on completion of each of the 3 month face to face interview and the 6 month telephone interview (see Figure 
1).

**Figure 1 Fig1:**
[figure not shown]
**Consort diagram for Kahungunu infant sleep study.**

### Eligibility

Eligible participants are all women booking for antenatal care from two midwifery practices working with mainly Māori women from low socio-economic areas in the Hawke’s Bay, who are resident in the Hawkes Bay District Health Board, and likely to remain in that area for at least six months.

